### Patients and recruitment

2.2

The recruitment goal is to include a total of N=144 female patients with planned gynecology laparoscopy. To this end, women between 18 and 70 years of age and an ASA Classification from I–III are recruited before the surgery in the department of Anesthesiology and Intensive Care Medicine at the University Hospital Essen, Germany and in the department of Anesthesiology at the University Medical Center Hamburg Eppendorf, Hamburg, Germany.

As part of the standardized recruitment process, we review the operating schedules of the hospitals in advance and consult with the respective gynaecology departments regarding potential candidates. Patients are offered participation in the study during the premedication visit. Exclusion criteria include any acute major psychiatric illnesses (severe episodes of anxiety, affective disorders, psychosis, or acute exacerbations of substance abuse), a suspected highly malignant tumor requiring surgery to remove one or more than one organ, benzodiazepines in long-term medication defined as regular daily intake according to the medication plan at least one month, previous serious anesthesia-related complications (e.g. difficult airway with anesthesia problem card), expected difficult airway leading to fiberoptic awake intubation as a particularly anxiety-inducing procedure or rare hereditary galactose intolerance, lactase deficiency or glucose-galactose malabsorption due to the ingredients of the placebo pill. In addition, an insufficient proficiency in the German language and in retrospect severe peri- and postoperative complications (e.g. life-threatening condition with unplanned admission to the intensive care unit or death) leading to exclusion. History of drug use and abuse is taken during the premedication visit and taken into account for our study.

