### Study procedures

2.4

Patients undergoing elective gynecological laparoscopy at the University Hospitals of Hamburg and Essen are offered to participate in the study. After consultation with an anesthesiologist who is not involved in the study, patients are informed about the study, clinically examined and informed consent is obtained by a study physician, an experienced anesthesiologist. In all groups, information about the study is provided by the study physicians in the premedication outpatient clinics individually, which is typically one to five days before the surgery at both study sites.

Patients are assessed at 5 predefined time points. After informed consent, patients complete a comprehensive questionnaire battery (T1). This package includes information on demographics, state and trait anxiety, pain level over the past 4 weeks, treatment expectations regarding to the upcoming surgery and, if applicable, expectations concerning OLP (for details see 3.5). Patients will complete a short questionnaire at the beginning and at the end of the consultation with the study physician, about their current anxiety and treatment expectations in order to assess the impact of the study physician’s suggestions, including the rationale for OLP. Additionally, the patients rate the warmth and competence of the study physician using a standardized questionnaire. Patients in the OLP+V-Group watch the video after the consultation with the study physician and are also subsequently asked to answer questions about their perception of the video.

At the time the patients are called to the operating room, approximately 45 minutes before the start of surgery (T2), patients randomized to the OLP groups receive OLPs from the nursing staff. In addition, the patients evaluate their preoperative anxiety. Just before the induction of anesthesia in the preoperative phase (T3), preoperative anxiety is assessed again. In addition, the anesthetist subjectively assesses the patients’ level of calmness or anxiety. After surgery in the recovery room, patients are asked about their current level of anxiety and about their current pain level for visceral and somatic pain modalities (T4).

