On the first postoperative day (T5), patients report if they took the OLPs, their current anxiety and retrospectively their anxiety before surgery. They assess mobility and their general condition. Current pain, visceral and somatic pain modalities as well as discomfort are also recorded. In addition, the warmth and competence of the anesthesiologist performing anesthesia in interacting with the patient and the patient’s perspective on the acceptability of OLPs is recorded.

The patients in the TAU-Group also receive the questionnaires at the same time points, and otherwise no differences from standard care are made. Patients can withdraw their participation in the study at any time.

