### Data analysis

2.7

A power analysis calculated with G*Power (version 3.1.9.6) resulted in a sample size of 120 patients for an expected small to medium effect size f of 0.2, two measurement time points, three groups, a significance level of α=0.05 and a power of 0.95. In order to be able to take possible exclusions during the course of the study into account, 20% more patients will be recruited, so that the final sample size is N=144 women. The effect size was derived from our own data and the literature after careful consideration with experts and colleagues at the two university hospitals. A medium to small effect size was chosen in order to be able to investigate small effects.

To analyze the main outcome (object 1), preoperative anxiety (APAIS), we will perform a univariate analysis of variance (ANOVA) with *post hoc* tests to determine differences in anxiety before surgery in the three groups. To analyze the dynamic changes of anxiety in the different groups before and after open placebo administration (TAU, OLP and OLP-V), repeated measures analyses of variance followed by *post hoc* tests are performed (object 2). In addition, ANOVAs will be conducted to assess postoperative pain (NRS) and other clinical characteristics by group (object 3). Patient and staff reports are primarily analyzed descriptively and free-text qualitatively (object 4). Furthermore, correlation and regression analysis will be used to identify exploratory predictive patient characteristics (object 3 & 4). No interim analysis is planned. If data is only available from one patient at three or fewer time points, the patients are excluded from the analysis.

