**Figure 2 f2:**
[figure not shown]
Graphical overview of the expected results. TAU, treatment as usual; OLP, open-label placebo; OLP+V, open-label placebo + video.

Objective 1: To compare preoperative anxiety after standard treatment (TAU-Group) against modulation of treatment expectations using OLP (OLP-Group) and to determine whether the effects after modulation of treatment expectation using OLPs can be enhanced by a video with aspects of verbal suggestion and observational learning (OLP+V-Group).

We postulate a lower level of preoperative anxiety in the OLP groups compared to treatment as usual, e.g. the provision of information as part of the anesthesiological consultation, with the greatest effects in the OLP+V-Group (**Figure 2**). Therefore, we analyze the self-reported preoperative anxiety (APAIS), to determine differences in anxiety immediately before surgery across the three groups. Previous studies, such as those by Schaefer et al. (30, 59), and Buergler et al. (60), demonstrate the effectiveness of OLP in modulating negative emotions, such as anxiety and stress (30, 59, 60). In a study with test anxiety as the primary outcome, Schaefer et al. demonstrated how the use of OLPs could successfully contribute to its reduction in students (30). The same working group presented that self-reported lower emotional distress when viewing highly arousing negative pictures in the OLP-Group was associated with activation of brain regions known to modulate affective states, such as the hippocampus and periaqueductal grey (59). In turn, a positive correlation between anxiety and OLP response has already been shown, with gastrointestinal-specific anxiety beeing a predictor of response to OLPs in patients with irritable bowel syndrome (38). Therefore, we expect a reduced level of preoperative anxiety in the OLP groups. It should be noted, that the literature does not indicate the minimum clinically significant difference for the APAIS or anxiety on an NRS, therefore it should be considered that a statistically significant result does not necessarily imply clinical significance.

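### Two exclusion rules remove randomised patients from the analysis on events that can follow the primary outcome, discarding valid primary data and leaving room for bias between arms

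*Protocol article*

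**What the plan says.** All references are to the protocol article.

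- **Visits (2.4 Study procedures).** "Patients are assessed at 5 predefined time points". T1 follows consent and T2 is the call to the operating room. For T3: "Just before the induction of anesthesia in the preoperative phase (T3), preoperative anxiety is assessed again". For T4: "After surgery in the recovery room, patients are asked about their current level of anxiety". For T5: "On the first postoperative day (T5), patients report if they took the OLPs". So T1 to T3 precede surgery, and T4 and T5 follow it.
- **Primary outcome (2.7 Data analysis; section 3, Objective 1).** "To analyze the main outcome (object 1), preoperative anxiety (APAIS), we will perform a univariate analysis of variance (ANOVA") with post hoc tests. Section 3 gives the purpose as "to determine differences in anxiety immediately before surgery across the three groups".
- **Rule A (2.7).** "If data is only available from one patient at three or fewer time points, the patients are excluded from the analysis".
- **Rule B (2.2 Patients and recruitment).** The exclusion list includes "in retrospect severe peri- and postoperative complications (e.g. life-threatening condition with unplanned admission to the intensive care unit or death) leading to exclusion".
- **Order of events (2.4.2 Blinding).** Randomisation comes before informed consent, so both rules act on patients already allocated to an arm.
- **Allowance (2.7).** 120 patients are increased by 20% to 144 to cover exclusions during the study.

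**The concern.** The primary analysis compares anxiety recorded before surgery. Rule A makes entry to that comparison depend on questionnaires completed after surgery. Rule B makes it depend on complications, which can also occur after the anxiety rating exists. Neither rule exempts Objective 1.

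Two things are at stake. First, valid primary data are discarded for reasons unrelated to whether the outcome was measured, and the groups compared are no longer those formed by randomisation. Secondly, selection after randomisation can bias the comparison if it relates to anxiety differently by arm. The article leaves room for that. Patients, study physicians and ward nurses know whether an open-label placebo is given (2.4.2), and section 3, Objective 3, itself links preoperative anxiety to intraoperative complications.

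**Working it through.** **1. The plan's own figures.** 120 × 1.2 = 144, as stated. The 120 reproduces as a repeated-measures within-between interaction with k = 3 groups, m = 2 measurements and f = 0.2, if the unstated correlation ρ is taken as 0.4: λ = f²Nm/(1−ρ) = 0.04 × 120 × 2 / 0.6 = 16, on 2 and 117 df, power 0.952. With ρ = 0.3 it would be 141, and with ρ = 0.5 it would be 102. The point below does not depend on ρ. The allowance budgets for 144 − 120 = 24 exclusions, or 24/144 = 16.7%.

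**2. Rule A applied pattern by pattern.** A patient needs data at four or more of five time points.

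| T1 | T2 | T3 | T4 | T5 | Count | Rule A |
|---|---|---|---|---|---|---|
| yes | yes | yes | no | yes | 4 | kept |
| yes | yes | yes | no | no | 3 | dropped, although all preoperative data exist |
| yes | yes | no | yes | yes | 4 | kept, although the last preoperative rating is absent |

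The rule does not track whether the primary outcome was recorded.

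**3. How many patients.** The documents give no missingness rates, so these are assumptions: T1 complete, visits missing independently, p = 5–10% at each of T2 and T3, q = 10–30% at each of T4 and T5.

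- Excluded = 1 − P(none missing) − P(exactly one missing) over T2 to T5.
- Excluded with T3 present = (1−p) × P(at least two of T2, T4, T5 missing).
- Excluded with T1 to T3 complete = (1−p)²q².
- Kept without T3 = p(1−p)(1−q)².

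| p | q | Excluded | of which T3 present | of which T1–T3 complete | Kept without T3 |
|---|---|---|---|---|---|
| 5% | 10% | 3.0% | 1.8% | 0.9% | 3.8% |
| 10% | 10% | 5.2% | 2.5% | 0.8% | 7.3% |
| 5% | 30% | 13.2% | 10.5% | 8.1% | 2.3% |
| 10% | 30% | 17.5% | 11.9% | 7.3% | 4.4% |

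Example, last row: P(none) = 0.9² × 0.7² = 0.3969; P(one) = 2(0.1)(0.9)(0.49) + 2(0.3)(0.7)(0.81) = 0.4284; excluded = 0.1747, or 25 of 144. Rule B would add to this by an amount the documents do not allow one to estimate.

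**4. Precision.** If all 24 budgeted patients are lost, the power of the one-way primary ANOVA at f = 0.2 (λ = f²N) falls from 0.556 at N = 144 to 0.476 at N = 120.

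**5. Bias.** Simulation under no true effect: 48 per arm, 4000 runs, standard normal anxiety. Exclusion follows a logistic model, with the stated probability at mean anxiety and a log-odds slope per SD of anxiety. The shift is the mean of the two OLP arms minus TAU, in SD; negative favours OLP.

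| Slope (TAU / OLP / OLP+V) | Shift at 5% / 10% / 16.7% | Type I error at 5% / 10% / 16.7% |
|---|---|---|
| 0 / 0 / 0 | 0.005 / 0.002 / 0.005 | 0.044 / 0.050 / 0.052 |
| 0.7 / 0.7 / 0.7 | 0.004 / −0.007 / 0.002 | 0.044 / 0.045 / 0.053 |
| 0 / 0.7 / 0.7 | −0.041 / −0.078 / −0.123 | 0.055 / 0.064 / 0.074 |
| 0 / 1.1 / 1.1 | −0.078 / −0.139 / −0.196 | 0.065 / 0.099 / 0.139 |
| −0.7 / 0.7 / 0.7 | −0.080 / −0.154 / −0.249 | 0.066 / 0.104 / 0.196 |

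In arms with slope 0.7, average exclusion is slightly above the nominal value (6.1%, 11.7% and 18.8%). The simulation error of a type I rate near 0.05 is about √(0.05 × 0.95/4000) = 0.003. Reversing the slopes would reverse the sign of the shift.

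**The case against.** Several objections have force and limit the claim.

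- **One missed visit is not enough.** With T1 to T3 complete, both T4 and T5 must be absent, and T4 is collected by staff on paper in the recovery room (2.6). A reader might infer that an OLP patient who declines the day-1 placebo questions is thereby excluded. She is not: T5 also collects anxiety, pain, mobility and general condition, and losing T5 altogether still leaves four time points.
- **The blinding is better than none.** Anaesthesiologists and gynaecologists in routine care are described as fully blinded, and data entry and quality control precede unblinding. Rule A is a mechanical count. Discretionary exclusion by arm is not shown. Differential non-response remains possible, because patients, study physicians and ward nurses know OLP status.
- **Safety.** A reader might infer that excluding intensive-care admissions and deaths conceals them. The article says such patients are excluded; it does not say they go unreported, and safety reporting is commonly left to the full protocol.
- **Which visit carries the APAIS.** Section 2.4 places preoperative anxiety ratings at both T2 and T3 without saying which holds the primary APAIS. So a patient kept without T3 need not lack the primary outcome, and if she does, the ANOVA simply omits her. That pattern is no error in itself.
- **Another count exists.** Section 3, Objective 2, lists four occasions up to induction. Were Rule A to count those, a patient with complete preoperative data would stay. But that list belongs to Objective 2, while 2.4 defines the trial's five time points, so the five-point reading is the natural one.
- **The 20% allowance and rarity.** The allowance protects precision but does not address bias. Rule B events are probably few in elective laparoscopy (an assumption), so Rule A is likely to matter more.

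None of this supplies a reason for a preoperative primary ANOVA to depend on postoperative data.

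**Conclusion.** The point holds. Both rules are stated in the article, so this is not detail left to an unseen analysis plan. For any randomised patient who has a preoperative APAIS and is caught by either rule, a valid primary observation is lost and the comparison as randomised is broken; that much needs no assumption.

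The number affected is unknown. On the assumed rates it is about 3–17.5% excluded under Rule A, 2–12% despite a T3 rating.

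Bias is possible rather than demonstrated. Under no true effect it is about zero when exclusion acts alike in all arms, and roughly 0.04–0.12 SD with type I error 0.055–0.074 under moderate OLP-only dependence at 5–16.7% exclusion. At 16.7%, only the stronger or opposite-direction dependence gives shifts of 0.20–0.25 SD and type I error of 0.14–0.20. These figures rest wholly on the assumed exclusion model.

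**What to change.** Replace both rules for Objective 1 with a statement to this effect: *all randomised, consenting patients with a preoperative APAIS rating are analysed in their allocated arm, regardless of missing data at T4 or T5 and regardless of complications during or after surgery.* In addition:

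- state which time point carries the primary APAIS;
- for Objectives 2 and 3, use all available ratings;
- keep the time-point rule and the complication rule only as labelled sensitivity analyses, and say which occasions the time-point rule counts;
- report severe complications by arm.

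The cost is wording and a small amount of extra analysis. No new data or patients are needed, and the primary analysis gains the patients now dropped.

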## Anticipated results

3

Given the background and the specific aims, we expect the following results based on the planned hypothesis testing of the data collected as part of the PATE Trial. A symbolic illustration of the expected group differences in the level of anxiety in the three study groups can be found in **Figure 2**.

**Figure 2 f2:**
[figure not shown]
Graphical overview of the expected results. TAU, treatment as usual; OLP, open-label placebo; OLP+V, open-label placebo + video.

Objective 1: To compare preoperative anxiety after standard treatment (TAU-Group) against modulation of treatment expectations using OLP (OLP-Group) and to determine whether the effects after modulation of treatment expectation using OLPs can be enhanced by a video with aspects of verbal suggestion and observational learning (OLP+V-Group).

We postulate a lower level of preoperative anxiety in the OLP groups compared to treatment as usual, e.g. the provision of information as part of the anesthesiological consultation, with the greatest effects in the OLP+V-Group (**Figure 2**). Therefore, we analyze the self-reported preoperative anxiety (APAIS), to determine differences in anxiety immediately before surgery across the three groups. Previous studies, such as those by Schaefer et al. (30, 59), and Buergler et al. (60), demonstrate the effectiveness of OLP in modulating negative emotions, such as anxiety and stress (30, 59, 60). In a study with test anxiety as the primary outcome, Schaefer et al. demonstrated how the use of OLPs could successfully contribute to its reduction in students (30). The same working group presented that self-reported lower emotional distress when viewing highly arousing negative pictures in the OLP-Group was associated with activation of brain regions known to modulate affective states, such as the hippocampus and periaqueductal grey (59). In turn, a positive correlation between anxiety and OLP response has already been shown, with gastrointestinal-specific anxiety beeing a predictor of response to OLPs in patients with irritable bowel syndrome (38). Therefore, we expect a reduced level of preoperative anxiety in the OLP groups. It should be noted, that the literature does not indicate the minimum clinically significant difference for the APAIS or anxiety on an NRS, therefore it should be considered that a statistically significant result does not necessarily imply clinical significance.

We hypothesize that the effect is pronounced in the OLP+V-Group, as the video with aspects of verbal suggestion and observational learning is particularly effective in reducing anxiety. Verbal suggestion and observational learning are important psychological mechanisms underlying positive and negative expectancy effects with great potential for clinical applications. Building on our previous work with expectation manipulation in chronic low back pain, e.g. observing a sham actor patient mimicking the benefits of pharmacological treatment (in this case amitriptyline) on function (42), we aim to support these findings in patients undergoing surgery. As there has been no study to date of OLP and observational learning in patients undergoing surgery, we aim to address this gap, given the potential benefits of using it in a video format in clinical practice.

Objective 2: To compare dynamic changes in anxiety and treatment expectations in the three groups.

In the context of the modulation of treatment expectations, we assume that not only the administration of the OLP alone, but rather the entire psychosocial treatment context, in particular the doctor–patient interaction, is pivotal. Therefore, we are interested in the dynamic changes in both preoperative anxiety and treatment expectations over time. Hence, we will analyze the course of self-reported anxiety based on the anxiety ratings (NRS) and treatment expectations (SETS) for the four time points, before and after OLP information, on the ward and directly before induction of anesthesia. We expect that the detailed consultation with the study physicians and the explanation of the rationale of the OLP will reduce patients’ preoperative anxiety and positively modulate their expectation.

Objective 3: Comparison of group differences in the pre- and postoperative course, in particular visceral and somatic postoperative pain intensity, sedative, anesthesia and analgesic requirements, duration of anesthesia induction and hospital stay.

Preoperative anxiety is associated with the risk of intraoperative complications and the need for sedation (5). It also impacts on postoperative outcomes (6, 7, 61), especially the pain experience (8, 9).

In addition to reduced anxiety, we expect that patients in the OLP-Group will require less benzodiazepine rescue medication. In the postoperative period, we expect patients in the OLP groups to report less pain than those in the TAU-Group. A difference of at least 1 point on the NRS is considered a clinically relevant difference, as the MCID for acute pain management is based on a systematic review of at least 8 mm on a VAS scale (62). Our assumption is based on the close relationship between anxiety and pain (8, 9). In particular, visceral pain is associated with anxiety and negative emotions (63), leading us to hypothesize that visceral pain will be particularly reduced with OLP. Exploratively, we will examine analgesic consumption in the PACU and postoperatively on the ward, as reduced preoperative anxiety may be associated with reduced postoperative opioid consumption. We also aim to assess whether there are group differences in patients’ reported self-efficacy and the appropriateness of placebo use in the clinical context from the patient’s perspective.

Objective 4: To explore the patient and healthcare providers perspective regarding the use of OLPs to reduce anxiety before surgery.

Research on open-label placebo in the clinical context remains novel, meaning there is little data on the patient and healthcare provider perspective. To date, quantitative research in clinical populations is lacking and the healthcare provider perspective, e.g. those who administer OLPs, has not yet been captured (43, 44, 64).

Therefore, one aim of this study is to explore patients’ views on the effectiveness and appropriateness of OLPs before surgery in a large clinical population. Firstly, we investigate the effectiveness of OLPs from the patient’s perspective post-surgery. We further intend to gain an understanding of whether patients consider OLP administration to be critical in the context of surgery or are open to it, thus asking their opinion on the application in this and other situations. In addition, we plan to interview the TAU-Group who have not received OLPs for their views on the application of OLPs. In addition to the patient perspective, we include the health care providers opinion on patients’ benefit from taking OLPs.

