Therefore, we designed a bicentric randomized-controlled clinical trial dedicated to elucidate the optimization of treatment expectations using OLPs to reduce preoperative anxiety and to improve postoperative outcomes in gynecological patients. Patients will be randomized into three groups prior to laparoscopic gynecological surgery. The design allows for testing the effects of the OLP versus standard care. In addition, we will test whether the effects of OLP can be enhanced by social observational learning, e.g. via a video presenting information about OLP from a satisfied patient. The primary outcome will be preoperative anxiety. Secondary outcomes will include postoperative visceral and somatic pain, sedation requirements and analgesic consumption. Additionally, the perspectives of patients and healthcare providers on the use of OLPs will be evaluated.

Specific objectives of this study:

Objective 1: To compare preoperative anxiety after standard treatment (TAU-Group) against modulation of treatment expectations using OLP (OLP-Group), and to determine whether the effects after modulation of treatment expectation using OLPs can be enhanced by a video with aspects of verbal suggestion and social learning (OLP+V-Group).Objective 2: To compare dynamic changes in anxiety and treatment expectation over time in the three groups.Objective 3: Comparison of group differences in the pre- and postoperative course, in particular patient-reported visceral and somatic postoperative pain intensity, sedative, anesthesia and analgesic requirements, duration of anesthesia induction and hospital stay.Objective 4: To explore the patients and health care providers perspective regarding the use of OLPs to reduce anxiety before surgery.

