#### Postoperative pain

2.5.4

Postoperatively at T4 and T5, patients indicate their pain at rest and during movement (NRS 0–10; 0 – No pain at all; 10 – Highest pain imaginable). In addition, based on previous studies (23, 56), patients rate their pain based on localization, which includes “deep abdominal pain,” which is described as dull, cramping, and difficult to localize, and is indicative of visceral pain, usually from internal organs. In contrast, “superficial wound/scar pain” is described as somatic pain, which is typically more localized and associated with the skin, muscle or connective tissue around the surgical wound or suture (both assessed on Visual Analogue Scales (VAS 0–10; 0 – No pain; 10 – Highest pain imaginable). Furthermore, we record the subjective perception of pain relief and satisfaction with the pain therapy using the NRS.

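### The claim that OLP reduces visceral pain more than somatic pain is not tested by the stated by-group ANOVAs; it needs a within-patient contrast between arms

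*Protocol article*

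**What the plan says.** The Introduction makes both pain modalities secondary outcomes: "Secondary outcomes will include postoperative visceral and somatic pain". It also argues that visceral pain in particular is amplified by negative emotion, and sets it against superficial somatic pain.

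Section 2.5.4 has patients give two sets of ratings at T4 and T5. Pain at rest and on movement is rated on an NRS. Deep abdominal (visceral) and superficial wound (somatic) pain are "both assessed on Visual Analogue Scales" running from 0 to 10.

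Section 3, Objective 3, first expects less pain in the OLP groups than under TAU and gives a relevance threshold: "A difference of at least 1 point on the NRS is considered a clinically relevant difference". It then adds the modality hypothesis, "leading us to hypothesize that visceral pain will be particularly reduced with OLP".

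Section 2.7 gives the analysis for this objective: "ANOVAs will be conducted to assess postoperative pain (NRS) and other clinical characteristics by group (object 3". Repeated-measures ANOVA is mentioned only for Objective 2: "To analyze the dynamic changes of anxiety in the different groups before and after open placebo administration". Correlation and regression are reserved for exploratory patient predictors.

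**The concern.** A larger effect on visceral than on somatic pain is a group-by-modality interaction. Both scores come from the same patient, so the quantity of interest is how far the within-patient gap between them differs by arm. A by-group ANOVA of visceral pain tests whether arms differ on visceral pain, and one of somatic pain does the same for somatic pain. Neither estimates the difference between the two effects.

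Followed as written, the plan leaves the hypothesis untested. The only material left for judging it would be two separate test results, and a significant result beside a non-significant one does not show that the effects differ. Visceral and somatic pain are the postoperative outcomes singled out in the Abstract and Conclusions, so a visceral-specific statement would probably feature in the report.

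**Working it through.** **1. Does any stated analysis address the claim?** Write V and S for a patient's visceral and somatic VAS. The hypothesis concerns [mean V in OLP − mean V in TAU] − [mean S in OLP − mean S in TAU], which equals the between-arm difference in the mean of D = V − S. Section 2.7 offers by-group ANOVA for pain, repeated measures for anxiety, and regression for predictors. None of these, as described, contains D or a modality factor. This step needs no assumed figure.

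**2. Group sizes.** Section 2.7 "resulted in a sample size of 120 patients for an expected small to medium effect size f of 0.2", with "two measurement time points, three groups, a significance level of α=0.05 and a power of 0.95". The number 120 can be recovered from the within-between interaction form with an unstated correlation of about 0.40: λ = f²·N·m/(1−ρ) = 0.04 × 120 × 2 / 0.60 = 16, with 2 and 117 df, gives power 0.952. The present point does not depend on that correlation; it uses only the sizes. These are 120/3 = 40 per group evaluable and, with the 20% addition, 144/3 = 48 per group recruited (equal allocation assumed).

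**3. What would two separate ANOVAs show if both effects were equal?** The document gives neither a pain SD nor a visceral-somatic correlation, so these are assumed: SD 2.0 or 2.5, correlation 0.3 to 0.7, equal SDs, normal scores, the same effect in both OLP arms. The article's 1-point threshold then equals 1/2.0 = 0.5 SD or 1/2.5 = 0.4 SD. The planning value f = 0.2 corresponds to 0.2 × 3/√2 = 0.42 SD when both OLP arms differ equally from TAU. Three-arm ANOVAs at α = 0.05, 40,000 simulated trials per setting:

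| Per group | True effect on both | Power of each ANOVA | Visceral only significant (ρ = 0.3 / 0.5 / 0.7) | Group-by-modality test rejects |
|---|---|---|---|---|
| 40 | 1 point, SD 2.0 | 0.62 | 0.19 / 0.16 / 0.12 | 0.05 |
| 40 | 1 point, SD 2.5 | 0.43 | 0.20 / 0.17 / 0.13 | 0.05 |
| 40 | f = 0.2 | 0.47 | 0.21 / 0.17 / 0.13 | 0.05 |
| 48 | 1 point, SD 2.0 | 0.71 | 0.18 / 0.14 / 0.11 | 0.05 |
| 48 | 1 point, SD 2.5 | 0.50 | 0.20 / 0.17 / 0.13 | 0.05 |
| 48 | f = 0.2 | 0.56 | 0.21 / 0.17 / 0.13 | 0.05 |

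Extending the effect down to 0.3 SD keeps visceral-only results within 11-21%. The direct test rejects in 5% of trials, about half of them (2.5%) in the visceral direction. Counting results in either direction, exactly one modality is significant in 22-41% of these settings, but the somatic-only half would contradict the hypothesis rather than falsely support it.

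**4. What could the direct test detect?** SD of D = σ√(2(1−ρ)). For the pooled OLP arms against TAU, SE = SD_D × √(1/(2n) + 1/n). Example with σ = 2.0, ρ = 0.5, n = 40: SD_D = 2.0, SE = 2.0 × √(1/80 + 1/40) = 0.387. An extra visceral effect of 1 point gives 1/0.387 = 2.58 and power of about 0.73. Over SD 2.0-2.5, correlation 0.3-0.7 and 40-48 per group, power is 42-96% for an extra 1 point and 14-45% for an extra 0.5 point.

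**The case against.** The strongest reply is that the article never says selectivity will be read from two p-values. That is correct. A reader might infer that the trial will often announce a false visceral-specific effect, but the 11-21% applies only if someone draws that inference, and no section prescribes it. What stands is that the article offers no other basis for the claim.

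Second, the article is condensed and an unseen SAP could add an interaction term. Missing model detail would indeed be no finding. Here, though, a comparative hypothesis is stated and the type of analysis named for its objective answers a different question.

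Third, Objective 3 itself speaks of group differences, which by-group ANOVA does address, and the comparative reading turns on one adverb in Anticipated results. However, that adverb follows a separate expectation of less pain overall, and the rationale given is specific to visceral pain. The comparative reading is therefore the natural one.

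Fourth, a reader might infer that naming the NRS in section 2.7 mislabels the VAS scores. The documents do not support that: section 2.5.4 has NRS ratings at rest and on movement, which section 2.7 may correctly mean. The narrower point is that section 2.7 does not name the visceral and somatic VAS scores at all.

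Finally, section 4.1 admits that power was not set for subgroup analyses and that smaller effects may be missed. It does not address comparing modalities.

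**Conclusion.** The point holds as a mismatch between a stated hypothesis and the stated analysis, and that part rests on no assumed number. Its size is conditional: if a visceral-specific effect were inferred from one significant and one non-significant ANOVA, equal true effects would give that pattern in about 11-21% of trials, against about 2.5% for a direct test in the same direction. Those figures rest on effects of 0.3-0.5 SD, correlation 0.3-0.7, equal SDs, normality and 40-48 patients per group; neither the SD nor the correlation is in the document.

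The hypothesis is secondary. Nothing here touches the primary outcome, the sample size or the data collection. Nor do the documents support ranking T4 above T5 for this contrast, since section 2.5.4 measures both without an order.

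**What to change.** Add to section 2.7, for Objective 3, wording such as: the hypothesis of a larger effect on visceral pain is tested on the within-patient difference, visceral minus somatic VAS (0-10, rated at T4 and T5), compared between the three arms, equivalently a group-by-modality term; separate ANOVAs of each modality do not support a visceral-specific claim. Name the two VAS scores as the outcomes for these modalities alongside the NRS ratings, and say how T4 and T5 will be used.

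The cost is a few sentences and one model on data already collected, plus one more secondary test. Because its power is limited, especially for an extra effect of 0.5 point, the plan should say that the contrast is reported with its confidence interval and that a non-significant result is not evidence of equal effects. If the sponsor does not want this test, the alternative is to reword the hypothesis so that it claims only a reduction in visceral pain.
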